### Randomization and blinding

Participants who meet the inclusion criteria for the study will receive a code from the screening assessors in order to maintain participants’ confidentiality. An independent researcher unaware of the study characteristics will perform the randomization process. In order to randomly allocate the participants to one of the three conditions referred to above (face-to-face MBI + TAU, Internet delivered MBI + TAU, and TAU alone), a computer-generated random number sequence (https://www.randomizer.org/) will be used by means of a simple allocation strategy and a 1:1:1 rate. After informing the patients of the study characteristics, they will accept to participate before the random allocation and without knowing the condition to which they will be allocated. The researcher who administers baseline assessments will be blind to the patients’ treatment group. This researcher will be different from the one – also blinded – who administers the other measures throughout the study. Patients in the Internet-delivered MBI arm will complete all the measures online. GPs will be blind, but the face-to-face MBI therapist will not. Participants will not be blind to the treatment condition for ethical and practical reasons.

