### Study population, recruitment, and eligibility criteria

This randomized controlled clinical trial will be conducted from the Health Center of Arrabal in Zaragoza (Spain). Participants will be adult PC outpatients attended to by their corresponding General Practitioners (GP), and they will be recruited by GPs working in the different Health Centers in Zaragoza (Spain). The researchers who manage the study will go to the different Health Centers to explain the study and eligibility criteria to the GPs, and they will give them an information sheet containing the study characteristics.

When a GP identifies a potential patient, s/he will explain the study to him/her and inform him/her that s/he can refuse to participate or withdraw from the study at any time, without any negative effects on their professional relationship or on future treatments that might be offered to the participant in PC. If the patient is interested, s/he will have to come to the Arrabal Health Center to clarify any doubts about the study and sign an informed consent form. Then, the patient will undergo a clinical interview and fill out the paper-and-pencil screening survey describing his/her sociodemographic and clinical characteristics. This first data collection and screening will be performed by specially trained psychologists with the objective of assessing whether the participants meet the eligibility criteria to participate in the study. If the participant meets the inclusion criteria, an independent researcher will implement randomization by telephone to avoid predictability.

Inclusion criteria will be as follows: a) older than 18 years; b) DSM-5 diagnosis of Major Depression or Dysthymia or mild or moderate depression, expressed as a score between 5 and 14 on the Patient Health Questionnaire (PHQ) [35]; c) depressive symptoms present for at least 2 months; d) having a computer and Internet at home; e) being able to read and understand the Spanish language; and f) willingness to participate in the study and sign the written informed consent form.

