### Instruments

The evaluations will be performed at screening, baseline, post-treatment, and 6- and 12-month follow-ups. All variables and assessment periods of the study can be found in Table 1. Scores on depression, negative and positive affect, and opinions about the modules will also be obtained after each completed module in the face-to-face and Interned-based MBIs. Participants in the TAU group will report their general opinion about the treatment as usual received at the end of the program.

**Table 1 Tab1:** Study outcomes

Instruments	Assessment Area	Time of assessment^a^
Sociodemographic	Gender, age, marital status, education, occupation, economical level.	Screening
MINI	Psychiatric diagnosis	Screening
PHQ-9	Severity of depression	Screening, post-module, post-treatment and follow-ups
CSRI	Health and social services use	Screening and 12-month follow-up
BDI-II	Severity of depression	Baseline, post-treatment and follow-ups
SF-12	Health-related quality of life	Baseline, post-treatment and follow-ups
EQ-5D	Health-related quality of life	Baseline and follow-ups
PANAS	Positive and negative Affect	Baseline, post-modules and follow-ups
FFMQ	Facets and factors of mindfulness	Baseline and follow-ups
PHI	Remembered and experienced well-being	Baseline and follow-ups
ETS	Treatment expectations	Baseline
OTS	Treatment opinions	Post-treatment

*MINI* Mini-International Neuropsychiatric Interview, *PHQ-9* Patient Health Questionnaire-9, *CSRI* Client Service Receipt Inventory, *BDI-II* Beck Depression Inventory-II, *SF-12* Short Form-12 Health Survey, *EQ-5D* EuroQoL-5D Questionnaire, *PANAS* Positive and Negative Affect Scale, *FFMQ* Five Facet Mindfulness Questionnaire, *PHI* Pemberton Happiness Index, *ETS* Expectation of Treatment Scale, *OTS* Opinion of Treatment Scale.

^a^Waves: screening, baseline, post-treatment (6 weeks for the “face-to-face MBI + TAU” and “TAU alone” or 12 weeks after baseline for the “Internet-delivered MBI + TAU”), post-module (after each individual module for the “face-to-face MBI + TAU” and for the “Internet-delivered MBI + TAU”), follow-ups (both 6 and 12 month follow-up measurements)

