#### Treatment expectations, opinions, and completion

##### -Expectation of treatment scale (ETS) and opinion of treatment scale (OTS)

These scales are adapted from Borkovec and Nau [61]. They include 5 items, rated from 0 (“not at all”) to 10 (“very much”), that address how logical the treatment seems, to what extent it satisfies the patient, whether it could be used to treat other psychological problems, its usefulness for the patient’s specific problem, and to what extent the treatment might be aversive. The expectation scale will be applied once the treatment rationale has been explained and after M0 to measure subjective patient expectations about the treatment they are about to receive. The opinion scale is administered when the patients have completed the treatment to assess their satisfaction with it.

In the case of the MBI groups, a question will be introduced related to the opinion about each individual module (e.g. “To what extent has this module been useful to you?“), using a visual analogue scale ranging from 0 (“nothing”) to 10 (“very much”), as well as two questions related to reviewing the materials (“Have you reviewed the last module seen in the session and all the materials it includes?”) and homework completion (“Have you done the tasks to train at home?”), with two possible responses (yes vs. no). In addition, a module completion register will be filled out.

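### The baseline and later researchers are called blind, but the article's own procedures do not secure this; GP blinding is stated without protection

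*Protocol article*

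**What the plan says.** The Randomization and blinding section assigns a blinding status to each role:

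- Baseline researcher: "The researcher who administers baseline assessments will be blind to the patients" (completed by a reference to treatment group).
- Later researcher: "This researcher will be different from the one – also blinded – who administers the other measures throughout the study".
- GPs and therapist: "GPs will be blind, but the face-to-face MBI therapist will not".
- Patients: "Participants will not be blind to the treatment condition for ethical and practical reasons".

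The same section adds: "Patients in the Internet-delivered MBI arm will complete all the measures online".

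Other sections fix the order and content of the assessments:

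- The eligibility section places allocation after screening: "If the participant meets the inclusion criteria, an independent researcher will implement randomization by telephone to avoid predictability".
- The Interventions section describes M0 for the two mindfulness conditions only, and places it ahead of the pre-treatment assessment.
- Table 1 lists the expectation scale (ETS) at baseline. Its own section says: "The expectation scale will be applied once the treatment rationale has been explained and after M0".
- Under Instruments: "Scores on depression, negative and positive affect, and opinions about the modules will also be obtained after each completed module". That sentence is limited to the two mindfulness arms. TAU patients instead give a general opinion on usual care at the end.

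**The concern.** A blinded assessor must be unable to tell the arm from the work that he or she is asked to do. Here the tasks given to both researchers appear to include material that differs by arm, so the article states a design property that its procedures may not deliver. A reader grading the trial for detection bias could credit it with assessor blinding.

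Two further matters are at stake:

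- If the pre-treatment assessment follows allocation and M0 in the mindfulness arms, the baseline BDI-II is a post-allocation measurement in those arms. The abstract adjusts the models for baseline scores, the main analysis standardises Cohen's d by the baseline SD, and the cost analysis measures effectiveness as change from baseline.
- GPs make the usual-care decisions that enter the cost outcomes. Under the eligibility section, a medication increase can also remove a patient from the analysis. It therefore matters whether GPs really remain unaware of allocation.

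**Working it through.** No figure in the plan depends on blinding, and the sample size calculation does not involve it. The check sets the sections side by side.

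**Step 1: is baseline after allocation?** Eligibility is established at screening and randomization follows. M0 is delivered in a format that depends on the arm, so the arm must be known before M0. M0 comes before the pre-treatment assessment. In the mindfulness arms the order is therefore screening, allocation, M0, pre-treatment assessment. This takes the pre-treatment assessment to be the baseline wave of Table 1; the flowchart is not shown. The Interventions section is inconsistent on whether the Internet arm's introductory session is in a group or individual. That must be reconciled, but on either reading the session belongs to the mindfulness arms only.

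**Step 2: which signals reach which researcher, and what do they reveal?**

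| Signal | Researcher, on a literal reading | Separates face-to-face from TAU? |
|---|---|---|
| M0 before the pre-treatment assessment | Baseline | Yes, if it comes up: TAU has no M0 |
| ETS after rationale and M0 | Baseline | By timing and context; the items are generic |
| Post-module scores and opinions | Later | Yes: none exist in TAU |
| Opinion of treatment at the end | Later | By content only; TAU patients give one too |
| Online completion | Both | No: identifies the Internet arm only |
| Post-treatment at 12 rather than 6 weeks | Later | No: identifies the Internet arm only |

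**Step 3: count the forms per researcher.** There are four therapeutic modules.

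- Baseline researcher: 1 form tied to the allocated treatment (ETS).
- Later researcher, face-to-face patient: up to 4 post-module forms + 1 opinion scale = 5.
- Later researcher, TAU patient: 0 + 1 = 1.
- Difference between the arms of the main comparison: 5 − 1 = up to 4 forms.

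Internet patients answer online. A patient who hands the later researcher a post-module form in person must therefore be face-to-face, and one who never does is likely to be TAU.

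**Step 4: GPs.** They recruit before randomization, so recruiting reveals nothing. Every arm receives TAU, so delivering it reveals nothing. No section has anyone tell them the allocation. They do go on treating patients who know their arm, and the article describes nothing to limit disclosure.

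**Step 5: the outcome.** The BDI-II total is the sum of the patient's answers, with no rater component described. What the assessor knows can affect it only indirectly.

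**The case against.** The strongest reply is that the article never says who collects the module forms. The wording of the review and homework questions, and the module completion register, are compatible with collection in session by the therapist, who is openly unblinded. A condensed article may leave such detail to the full protocol. This stands in part: leakage to the later researcher rests on a literal reading of a general phrase. But that phrase gives this researcher the remaining measures without exception. The baseline difficulty does not depend on it at all, since M0 and the ETS are placed in time by the article itself.

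It is also fair that the ETS items are generic and need not name an arm, and that self-report by unblinded patients is normal in a psychological-treatment trial and is disclosed here.

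Three stronger readings are tempting, and the document does not support them:

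- *GP blinding fails by construction.* Disclosure by patients is plausible, but it is a risk and not a stated procedure (step 4).
- *The article claims that assessor blinding protects the BDI-II.* It makes no such claim and says openly that participants are not blind. What can be said is that the listed limitations do not mention how little assessor or GP blinding does for a self-reported endpoint.
- *One assessor meets at least six arm-revealing contacts, and the online route exposes the main comparison.* A total of six combines two different researchers. The online route leaves face-to-face and TAU unresolved.

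**Conclusion.** The concern holds for the assessors. The stated blinding of the baseline researcher conflicts with the timing of M0 and the ETS. That of the later researcher is not secured if the assignment of measures is read as written. Both gaps reach the face-to-face versus TAU comparison. For GPs the documents support only this: they are not told the allocation, and nothing prevents them from learning it.

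The size of any bias cannot be derived. Through the assessor it is probably modest, because patients who know their arm answer the BDI-II themselves. The timing of the baseline may matter more. If M0 shifts the BDI-II, the shift enters the reference value in the mindfulness arms only. A fall after M0 would understate later change and a rise would overstate it; the direction is unknown.

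The conclusion assumes that the pre-treatment assessment is the baseline wave and that no fuller document assigns the arm-specific forms to someone else.

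**What to change.** 1. Reword Randomization and blinding. State that the BDI-II is self-reported by unblinded participants, that GPs are not informed of allocation but may learn it, and that assessor blinding is claimed only where the procedures support it.
2. Have the therapist or the existing web platform, not the outcome researcher, collect the ETS, the opinion scale, the post-module forms and the module register.
3. Have patients complete the BDI-II before any treatment-related item at each wave. Reconcile the baseline-blinding claim with the placement of M0, ideally by taking the baseline BDI-II before allocation and M0.

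The cost is protocol wording and a reassignment of forms among existing staff and platform; no extra patients are needed. The blinding claim becomes less favourable. The Study design section says recruitment is in progress, so items 2 and 3 apply only to the remaining assessments. The date of change should be recorded, because baselines taken before and after it would not be collected in the same way. The report should describe what was done for patients already assessed.

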### Sample size

The sample size estimation was based on testing whether the trend in the change is different between the intervention groups throughout the 4 time points. Firstly, we assumed that MBI groups would be able to present moderately high effects, compared to “TAU alone”, on the BDI-II at post-treatment. To operationalize this, we considered a standardized difference between arms on the main outcome of d = 0.7, which corresponds to the average effect observed in ten studies comparing MBIs with different wait-list conditions [36] and surpasses the 0.5 standard deviation criterion considered clinically relevant in previous studies [37, 38]. A preceding study by our research group with mild or moderate depressed patients in a similar Spanish PC setting found BDI-II means and standard deviations (SDs) of 22 and 5, respectively [20]. The inclusion criteria used in this study restricted the entry of mild or moderate depressed patients, thus reducing the SD compared to the general population and presenting a less skewed distribution of the data, as we predict will occur in the present study. The effect size referred to above corresponds to a difference of 3.5 points, which implies a reduction of slightly more than 15% in the BDI-II scale used. According to the GLIMMPSE v2.0.0 – time x group interaction in a general linear repeated measures (RM) design – and GPower v3.1.9.4 – ANOVA test for RM within-between interaction – statistical tools, considering the referred difference between the “face-to-face MBI + TAU” vs. “TAU alone” groups of depressed patients, which corresponds to a partial eta square value of roughly 0.09 and an effect size f of 0.31, with a common mean at baseline of 22, a mean at post-test of 16 and 19.5 respectively, and a mean at post-test of 17 for the “Internet delivered MBI + TAU” condition, and assuming a one point reduction in each group at each following time point, a baseline correlation of 0.6 and a decay rate of 0.35, assuming a common SD of 5, a 5% significance level, a statistical power of 80% using a 1:1:1 ratio, and an univariate approach to RM with Greenhouse-Geisser correction [39], we needed 33 subjects in each group. Because we expected a dropout rate of approximately 20% [40], we inflated the numbers to reach a total sample size of 120 patients, 40 per arm [41].

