The main hypothesis is that the MBI programs (face-to-face and online) will be more effective than TAU. Furthermore, improvements are also expected in secondary outcome measures (depression, positive and negative affect, and happiness) and other measures (health-related quality of life, mindfulness skills) in both intervention groups, compared to the TAU group. Additionally, the differences between face-to-face and online formats will be explored because, to our knowledge, there are no studies to date that compare MBIs applied online vs. face-to-face in this population. Finally, regarding cost-effectiveness, we expect that both MBI interventions will be more cost-effective than TAU. Additionally, cost-effectiveness differences between face-to-face and online formats will be explored.

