### Level of significance

An alpha level of 0.05 will be established using a two-tailed test. The probability values relative to the main analysis will be adjusted according to Benjamini-Hochberg’s correction for multiple comparisons, but the secondary and exploratory analyses will not be corrected.

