The limitations are similar to those of the study carried out by Castro et al. [10], who refer to possible negative attitudes from GPs about recommending this treatment, and high dropout rates in the treatment groups, especially in the control group. To minimize the effect of negative attitudes, the intervention characteristics will be explained in depth to the clinicians involved in the trial. In order to prevent dropouts, we will send emails to the participants reminding them to continue and complete the trial requirements. Another limitation is the possible small statistical power to obtain significant results in the comparison of the face-to-face and online MBI groups, but, as mentioned above, this study will be considered a pilot exploration of possible effect sizes to guide future research. Other difficulties that may appear could be related to recruitment because some people might not have access to the Internet at home, or they might even prefer traditional treatments (due to unawareness of the benefits of the new treatments and technologies) or be influenced by the depressive symptoms themselves (apathy, anhedonia, etc.).

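### The Internet programme is in the main hypothesis but was planned at d = 0.5, with about 50–69% power at 32 per arm and no disclosure; the dropout inflation to 40 per arm also falls one patient per arm short

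*Protocol article*

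**What the plan says.** All references are to the protocol article.

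- **Background (hypotheses):** "The main hypothesis is that the MBI programs (face-to-face and online) will be more effective than TAU".
- **Sample size:** the section begins by assuming a moderately high effect, d = 0.7, for the mindfulness groups against TAU. It then ties the calculation to the face-to-face versus TAU difference of 3.5 points and enters "a mean at post-test of 16 and 19.5 respectively, and a mean at post-test of 17 for the" Internet condition. It uses "a 5% significance level, a statistical power of 80% using a 1:1:1 ratio", a common SD of 5, a baseline correlation of 0.6 with decay 0.35, and a Greenhouse-Geisser-corrected time × group test. It concludes that "we needed 33 subjects in each group" and, for about 20% dropout, "we inflated the numbers to reach a total sample size of 120 patients, 40 per arm".
- **Main analysis and Secondary analysis:** face-to-face versus TAU on the BDI-II is the main analysis. Internet versus TAU is secondary.
- **Level of significance:** "An alpha level of 0.05 will be established using a two-tailed test". The main analysis gets a Benjamini-Hochberg adjustment, "but the secondary and exploratory analyses will not be corrected".
- **Discussion (limitations):** the only power caveat concerns the "possible small statistical power to obtain significant results in the comparison of the face-to-face and online MBI groups".

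**The concern.** Two things do not fit together.

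First, the allowance for dropout. Multiplying 33 by 1.2 gives 39.6, which rounds to the stated 40. That adds 20% to the target; it does not leave the target intact after 20% are lost.

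Second, the status of the Internet arm. The hypothesis and the opening of the sample-size argument treat both programmes alike. The mean actually entered for the Internet arm implies a smaller effect, the analysis sections demote the comparison, and the limitations do not mention its power.

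What is at stake is interpretation. If the planned Internet effect were true, a post-test comparison would miss it about half the time, yet the miss would count against a stated main hypothesis. A positive result would be an uncorrected secondary p-value supporting that same hypothesis.

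**Working it through.** **Inputs (Sample size section).** Means at the four time points, after applying the one-point fall per later visit: face-to-face 22, 16, 15, 14; Internet 22, 17, 16, 15; TAU 22, 19.5, 18.5, 17.5. SD 5; correlation 0.6 with decay 0.35; two-sided 5%; 80% power.

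**Assumptions made here.** Correlations follow the linear exponent autoregressive form, 0.6 raised to 1 + 0.35 × (lag − shortest lag)/(longest lag − shortest lag). The visit spacing used by the authors is not given, so three codings were run: equally spaced; months 0, 1.5, 6, 12; and months 0, 1.5, 7.5, 13.5. Ranges below span these.

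**1. Reproducing 33.**
- Three-arm interaction. Post-baseline deviations from the mean of 17.5 are −1.5, −0.5 and 2.0, with squares summing to 6.5. The interaction sum of squares is n × 0.75 × 6.5 = 4.875n, or 160.9 at n = 33. With equal spacing the error mean square is 10.84 and epsilon 0.98, so the noncentrality is 0.98 × 160.9/10.84 = 14.55 and power is 82.3%. Calendar spacing gives 80.5–80.7%. The required n is 32 or 33 per arm.
- Two-group t-test at d = 3.5/5 = 0.7. Noncentrality 0.7 × √(33/2) = 2.84; power 80.0%.

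The stated 33 reproduces by both routes.

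**2. Dropout.**
- 40 × 0.8 = 32, one below 33.
- 33/0.8 = 41.25, so 42 per arm and 126 in total.
- 1 − 33/40 = 17.5%, the loss that 40 per arm absorbs.

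**3. Internet effect.** 19.5 − 17 = 2.5 points; 2.5/5 = 0.5, not 0.7.

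**4. Internet versus TAU at 32 per arm.**
- Post-test t-test: noncentrality 0.5 × √(32/2) = 2.0; power 50.4%.
- Two-arm interaction: sum of squares 32 × 0.75 × 2.5²/2 = 75; with equal spacing, noncentrality 0.98 × 75/10.84 = 6.78; power 56.8%. The lowest calendar coding gives 55.0%.
- ANCOVA on baseline: residual SD 5 × √(1 − 0.6²) = 4; 2.5/4 = 0.625; noncentrality 0.625 × √16 = 2.5; power 69.2%.

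**5. All comparisons by completers per arm.**

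| Comparison | Method | 32 | 33 | 40 |
|---|---|---|---|---|
| Three arms | Interaction | 79.0–80.9% | 80.5–82.3% | 88.6–90.0% |
| Face-to-face vs TAU | Post-test t-test | 78.7% | 80.0% | 87.1% |
| | Interaction | 85.9–87.3% | 87.0–88.4% | 93.1–94.0% |
| | ANCOVA | 93.1% | 93.8% | 97.2% |
| Internet vs TAU | Post-test t-test | 50.4% | 51.6% | 59.8% |
| | Interaction | 55.0–56.8% | 56.4–58.3% | 65.8–67.7% |
| | ANCOVA | 69.2% | 70.6% | 78.8% |

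Table 1 places the Internet arm's post-treatment visit at 12 weeks rather than 6. Coding that visit at 3 months gives about 56% for the Internet interaction at 32 per arm, so the conclusion does not depend on it.

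**The case against.** The authors can fairly make four replies.

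- **The dropout slip hardly matters.** The rate is given only as approximate, and 17.5% is close to 20%. The loss is one completer per arm. The three-arm test at 32 falls just below or just above 80% depending on visit coding, and the planned mixed model uses partial data, so its power would lie between the 32 and 40 columns. This stands. A reader might infer that the trial as a whole misses its power target; the figures do not support that, least of all for face-to-face versus TAU, which exceeds 85% by both methods that use the baseline or repeated data.
- **No section promises 80% for Internet versus TAU.** A reader might infer such a promise from the hypothesis and the shared d = 0.7. But the calculation is expressly tied to face-to-face versus TAU, and the Internet comparison is openly secondary. This stands: the fault is inconsistency and non-disclosure, not a broken guarantee.
- **The sample size does serve the main test.** A reader might infer that 33 fits only the three-arm interaction, which is not the planned main comparison. It also fits a two-group test at d = 0.7, which is face-to-face versus TAU at post-treatment.
- **Leaving secondary analyses uncorrected is a disclosed choice.** That is so, and it is acceptable for a comparison that is secondary throughout. It sits badly only while the same comparison belongs to the main hypothesis.

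None of these replies reconciles the Background, Sample size, Secondary analysis and Discussion sections with each other on the Internet arm.

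**Conclusion.** The point holds in two parts of unequal weight.

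**Minor:** the inflation is arithmetically wrong. The target of 120 leaves 32 per arm at 20% dropout where 33 are required, six patients in total below the 126 that a 20% loss implies. The cost is about 1.5 points of power.

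**Substantive:** the Internet programme shares the main hypothesis and the opening d = 0.7 assumption, but was planned at d = 0.5. Its comparison with TAU has about 50–69% power at 32 per arm and 60–79% with no dropout at all, depending on method. No method tried reaches 80%, and the one power caveat in the article covers a different comparison.

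These figures rest on the plan's own means, SD and correlation, on the assumed correlation form and visit codings, and on complete cases. Twenty per cent is not evidently cautious: the Discussion anticipates high dropout, and the eligibility and TAU sections remove some further patients from the analysis.

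**What to change.** Change the text and keep 120.

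1. **Sample size:** state that 40 per arm leaves 32 at 20% dropout, or covers 17.5%, and give the resulting power: about 79–81% for the three-arm interaction, and for face-to-face versus TAU 79% (post-test t-test), 86–87% (interaction) or 93% (ANCOVA).
2. **Sample size:** state that d = 0.7 applies to face-to-face versus TAU, and that Internet versus TAU was planned at d = 0.5, with its power.
3. **Discussion:** extend the low-power limitation to Internet versus TAU.
4. **Background:** limit the main hypothesis to face-to-face versus TAU and list Internet versus TAU as secondary, matching the Main analysis and Secondary analysis sections.

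No change to the testing procedure is needed. The cost is wording, plus stated figures that are slightly less favourable and a narrower main hypothesis. No additional patients are required.
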